### Protecting against sources of bias

Participants, their parents, and the study RNs will be aware of group allocation as blinding is not feasible. However, clinical outcomes will be adjudicated by observers who are blind to group allocation (see Secondary outcomes #4 below). Furthermore, participants in both groups will be unaware of the primary outcome (excess time to attendance at first ACHD appointment) and therefore this outcome cannot be consciously influenced, though participants will be aware that the study will track information from the cardiology chart, including the first ACHD clinic visit. Clinic support staff and pediatric cardiologists will be blind to group allocation.

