## Methods

### Study design

The CHAPTER 2 Study is a two-center cluster randomized controlled trial of a nurse-led transition intervention versus usual care (see “usual care” section below). The intervention will consist of two individualized sessions lasting ~60 min each held two months apart, in or adjacent to the pediatric cardiology clinic. The study is registered with Clinical Trials.gov (ID NCT01723332) and will be conducted in accordance with CONSORT guidelines (Fig. 1) [19].

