### Transition intervention

The intervention will be conducted by one of two cardiology registered nurses (RNs) at each site (total 4 RNs) who are experienced working with teens. Youth will attend two one-on-one sessions with the same RN. Sessions will be youth-oriented, interactive, and engaging. Session One will occur immediately after a pediatric cardiology clinic visit to minimize study burden and to adhere with recommendations that transition interventions be delivered in clinical settings [21]. Individual sessions, in contrast to group sessions, allow the content to be patient-specific. Session Two will occur two months after Session One, in conjunction with another clinic appointment or as the sole purpose of a return visit. Individual participant flow through the study is illustrated in Fig. 2.

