	k) Accompany participant to the ACHD clinic	
	l) Provide study email address; encourage emails or text messages with RN. Questions posed to participants within 7 days:	
	1. “Where is your MyHealth passport now?”	
	2. “Have you used your MyHealth passport or shown it to anyone?”	
	3. “Do you have any questions for me?”	

*ACHD* adult congenital heart disease; RN: registered nurse

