### Group allocation

Participants will be randomized by clusters defined by week of attendance in the pediatric cardiology clinic. As week (not study participant) is the unit of randomization, this is a cluster randomization design. This method of randomization: 1) prevents two adolescents in the same waiting room being allocated to different groups and 2) facilitates scheduling of study RNs, who will be available at short notice to provide the intervention during intervention weeks. Cardiologists will not be informed of group assignment, preventing potential bias by cardiologist co-intervention. We anticipate enrollment of 3–4 patients per week, i.e., cluster size will be ≤ 4. To determine which weeks are “intervention weeks” vs. “usual care weeks”, a biostatistician will prepare a randomization sequence.

A 1:1 ratio of intervention: usual care weeks will be used until midway through enrollment, when there will be a re-evaluation. If there is an imbalance, then there will be an adjustment of the ratio of intervention to usual care weeks.

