### Secondary outcomes

Given the complex, multidimensional nature of the transition process, transition interventions need to consider multiple outcomes, including cognitive factors (e.g. CHD knowledge) and self-management behaviours. Therefore, several secondary outcomes are proposed. All baseline questionnaires will be completed in the pediatric clinic, and prior to Session One for those in the intervention arm.Change in MyHeart scores between baseline, 1, 6, 12 and 18 months. The MyHeart scale consists of eight questions that assess participant’s knowledge of their cardiac condition. The MyHeart scale was developed for the CHAPTER 1 study, with a significant improvement in score observed at 1 and 6 months post intervention, compared to participants in the usual care group [16].Change in Transition Readiness Assessment Questionnaire (TRAQ) score between baseline, 1, 6, 12, and 18 months. The TRAQ is the most rigorous transition readiness scale for adolescents. Sawicki et al. identified behaviours relevant to transition, tested item reliability and validity, and then field tested the items with 194 youth with special healthcare needs [18]. Scores range from 0 to 5. Principal component factor analysis revealed two domains explaining 68 % of the total variance: self-management (16 items, mean score 3.01 ± 1.02) assessing skills such as filling prescriptions, understanding treatment side effects, and arranging medical follow-up visits; and self-advocacy (13 items, mean score 3.67 ± 0.77) assessing communication skills with the healthcare team, managing activities of daily living, and use of school and community resources. Internal consistency is high, with Cronbach’s alpha of 0.92 (Self-management) and 0.82 (Self-advocacy). A ceiling effect is unlikely given the mean scores noted above. The reading level is Grade 5.7 and this instrument takes ~5 min to complete. The 12 and 18 month assessments will provide longitudinal data on evolution of self-management and self-advocacy skills and will allow participants in the intervention group sufficient time to apply the skills gained (e.g., to independently book a physician appointment).Change in the Williams’ Scale between baseline, 1, 6, 12, and 18 months. The Williams’ scale is a measure of medical self-management and transition readiness among adolescents with special health care needs, having high internal consistency (Cronbach’s alpha 0.89) [17]. This consists of 21 Likert-scaled items and has a grade 4.9 reading level.Assessment of patient engagement via a cardiologist questionnaire. This questionnaire will be completed by the participant’s primary cardiologist at the first cardiology clinic visit (pediatric or adult site), after month 3 post enrollment. This questionnaire will help determine if those participants in the intervention group were more engaged with their cardiologist then those in the usual care group. The single-page questionnaire consists of six items and takes 1–2 min to complete.Incidence of cardiac re-intervention (surgery or interventional catheterization). Chart review at 12 and 24 months post enrollment will be done independently by two RNs who will be blinded to group allocation. This review will ascertain cardiac hospitalizations and invasive cardiac procedures (since study enrollment), confirm attendance at ACHD clinic, and identify new or progressive complications (e.g., endocarditis, heart failure, stroke, thrombosis, systemic or pulmonary emboli, arrhythmia requiring drug or procedural intervention, renal or hepatic failure) [2]. Discrepant adjudication will be resolved by a cardiologist team member.Frequency and content of verbal and written (email/text messaging/telephone) dialogue between intervention nurse and participant. The intervention RN will complete detailed post-intervention field notes after each session. Telephone communication (phone calls, text messages) and emails will be encouraged from participants at any time; all will be recorded verbatim and analyzed (see Quantitative data analysis below).

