### Potential limitations

Several threats to internal validity exist. These include: (i) co-intervention; awareness of the study and of the need for health care transition may influence what cardiologists say to participants, however both groups will benefit equally and this will not create a bias towards one study group. Cardiologists will be unaware of group allocation. (ii) Loss to follow-up; when patients miss appointments, both Edmonton and Toronto ACHD clinics routinely use all available contact information to arrange another appointment and keep patients in care. From the perspective of the study, participants who have not attended the ACHD clinic by the end of the study period will be censored and will still contribute to the primary outcome. (iii) Provider/system factors such as waiting lists may influence the primary outcome. However this will be equally true of participants in both groups. The time interval between the *recommended* date of first ACHD appointment and *scheduled* date of first ACHD appointment will be recorded to capture provider/system factors. The mean wait time for non-urgent referrals to Canadian ACHD clinics is only 4 ± 2 months [29], so we do not anticipate this to be an issue. (iv) Responsiveness of the Williams’ transition readiness scale to intervention is not yet known, though this is just one of six secondary endpoints. Both the TRAQ and MyHeart scale are responsive to an educational intervention [16].

In summary, the CHAPTER 2 study is a two-center cluster randomized clinical trial of a nurse led transition intervention for 16–17 year olds with moderate or complex CHD. Fidelity of the intervention is a major focus and priority. We will evaluate time to first ACHD appointment, CHD knowledge, transition readiness, need for catheter and surgical re-intervention, and qualitative outcomes. The results of this study will inform pediatric cardiology programs, patients and policy makers in judging whether a structured intervention program provides clinically meaningful outcomes for adolescents and young adults living with CHD.

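### Blinding of cardiologists and clinic staff is asserted but not secured, which leaves the cardiologist-rated engagement outcome open to assessor bias

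*Protocol article*

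**What the plan says.** The section Protecting against sources of bias concedes that "Participants, their parents, and the study RNs will be aware of group allocation as blinding is not feasible" but adds that "Clinic support staff and pediatric cardiologists will be blind to group allocation". Group allocation gives the mechanism and its claimed effect: "Cardiologists will not be informed of group assignment, preventing potential bias by cardiologist co-intervention". Potential limitations repeats that cardiologists will not know the allocation.

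The procedures are these:

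- Study design places the two sessions as "held two months apart, in or adjacent to the pediatric cardiology clinic".
- Transition intervention puts Session One directly after the cardiology visit and says "Session Two will occur two months after Session One, in conjunction with another clinic appointment or as the sole purpose of a return visit".
- Table 1 has intervention participants create a MyHealth passport, and the nurse later asks: "Have you used your MyHealth passport or shown it to anyone".
- Secondary outcomes says of the engagement rating: "This questionnaire will be completed by the participant’s primary cardiologist at the first cardiology clinic visit (pediatric or adult site), after month 3 post enrollment". Its stated purpose is to see whether intervention participants were more engaged than usual-care participants.

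Protecting against sources of bias also says that clinical outcomes are adjudicated blind, and refers the reader to secondary outcome #4.

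**The concern.** Not being told is treated as being blind, and being blind as preventing bias. The plan describes nothing that would stop a cardiologist from learning the arm from the participant, a parent, the passport, or a nurse session in the same clinic.

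This matters most for engagement, because the cardiologist is the measuring instrument. If raters know or suspect the arm, part of any difference may be their expectation and not the participant's behaviour. As written, the report could present this result as protected by blinding.

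**Working it through.** **1. What is claimed and what supports it.** Three sections (Group allocation, Protecting against sources of bias, Potential limitations) claim unawareness. One mechanism is given: cardiologists are not informed. No separate room, booking route, instruction to participants or check on awareness is described.

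**2. What can reveal the arm before the engagement rating.**

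- Participants and parents are unblinded by the plan's own statement and talk to the cardiologist.
- Either session may be held in the clinic.
- Session Two, at two months, exists only in the intervention arm and may be combined with a clinic appointment.
- The passport exists only in the intervention arm, and the nurse's question anticipates that it will be shown to others.

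The rating falls after month 3. Session Two is scheduled for month 2, so on schedule every one of these cues precedes the rating.

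**3. Who the rater is.** The form may be completed at the pediatric or the adult site. The sentence in Protecting against sources of bias names pediatric cardiologists and clinic support staff only. Group allocation and Potential limitations say cardiologists without qualification. The status of adult-site raters is therefore unclear.

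**4. The cross-reference.** In the order of the Secondary outcomes section, the six are MyHeart, TRAQ, Williams' scale, cardiologist engagement questionnaire, re-intervention by chart review, and nurse–participant dialogue. Two other places confirm this numbering: Measurement of outcomes at follow-up treats outcomes 1–3 as participant questionnaires, and Potential limitations counts six secondary endpoints. So #4 is the cardiologist rating, while the review by two blinded nurses is #5. This is probably a numbering slip, but as printed the claim of blinded adjudication points at the engagement rating.

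**5. Illustration of sensitivity.** The plan gives no figure for rating bias, so the shift d below is my assumption. Inputs: 60 per arm (Proposed sample size), all assumed rated; two-sided 5% test; no true effect. The design effect (DE) is 1, or 1 + (4 − 1) × 0.05 = 1.15, taking four per week from Group allocation and an assumed intracluster correlation of 0.05.

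SE = √(2 × DE / 60), in SD units. False-positive rate = Φ(d/SE − 1.96) + Φ(−d/SE − 1.96).

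| Assumed shift d (SD) | DE = 1 (SE 0.183) | DE = 1.15 (SE 0.196) |
|---|---|---|
| 0.10 | 8.5% | 8.0% |
| 0.20 | 19.5% | 17.5% |
| 0.30 | 37.6% | 33.5% |

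These figures show how sensitive the comparison is. They do not predict that bias occurs.

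**6. The plan's power figure.** For 90% against 70%, the hazard ratio is ln(0.10)/ln(0.30) = 1.912 and the expected events are 60 × 0.9 + 60 × 0.7 = 96. Schoenfeld power is 88.8% before clustering and stays at or above 80% up to a design effect of 1.29. The stated power of 80% or more is thus reproducible for modest clustering, and nothing in this point alters it.

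**The case against.** The case for the plan has substance.

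- **Unblinding is not inevitable.** Session One follows the cardiologist's consultation, sessions may be beside the clinic, each site has several cardiologists, and at most four participants enrol per week. A condensed article may also leave out concealment logistics. This stands: a reader might infer that blinding cannot hold, but the documents show only that it is not secured.
- **Shared weeks do not reach the engagement rating.** A reader might reason that, once the week's first session is noticed, the other 2 of 3 or 3 of 4 participants (67–75%) are identifiable. That is an upper bound, and it concerns enrolment visits. The rating comes months later, so disclosure, the passport and Session Two are the likelier routes.
- **Loss of primary-outcome power is not shown.** A reader might suppose that cardiologists compensate usual-care patients. If attendance there rose from 70% to 72.5% or 75%, Schoenfeld power before clustering would fall from 88.8% to 81.5% or 71.4%. The arithmetic is right, but the lift is invented, usual-care weeks show no session to recognise, and no document suggests compensation. The cardiologist does set the recommended interval subtracted in the primary outcome, but nothing indicates that it would differ by arm.
- **The equal-benefit argument is about something else.** The statement in Potential limitations that "both groups will benefit equally and this will not create a bias towards one study group" concerns awareness of the study and of the need for transition, not awareness of allocation. It need not be withdrawn on this ground.
- **Accompaniment to the adult clinic** is listed in Table 1 under Session 1 and is not tied to the rating visit, so I give it no weight.
- **Some of what the rater sees is treatment effect.** Assertive behaviour or use of the passport is what the intervention aims to produce. Only expectation beyond the behaviour observed is bias.

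What survives is that *blind* and *preventing* overstate what not informing can deliver, for an outcome that depends on the rater's judgement.

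**Conclusion.** The point holds in a limited form. Blinding of cardiologists and clinic staff is stated as a fact, but it rests only on not telling them, while the plan's own procedures give them ways to find out. The consequence falls on one of six secondary outcomes, the cardiologist-rated engagement questionnaire, and is compounded by the unclear status of adult-site raters and by the #4 reference.

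The size of any bias is unknown. The illustrative 8.5% to 38% false-positive range rests on assumed shifts of 0.10 to 0.30 SD, 60 rated per arm and no clustering. Sample size and primary-outcome power are unaffected on the evidence in the documents. The re-intervention and ACHD-attendance chart review by blinded nurses stands.

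**What to change.** 1. **Conduct.** Hold both sessions beside the clinic and not in it, which Study design already permits. Have the site's project coordinator book Session Two.
2. **Form.** Add one item at the end of the cardiologist questionnaire, after the ratings, asking whether the rater knows or suspects the participant's group. Report the answers by arm. Do not restrict the analysis to unaware raters, because awareness arises after randomisation.
3. **Wording.** In Group allocation, Protecting against sources of bias and Potential limitations, replace the claims of blinding, unawareness and prevention with *not informed, but may infer*. State whether adult-site raters are informed of allocation. Point the blinded-adjudication reference to the chart review.
4. **Reporting.** Describe engagement as rated by assessors who may be aware of the group.

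The cost is a room and booking instruction, one question on an existing single-page form, and text edits. The sample size and primary analysis stay as they are. The downside is that engagement can no longer be presented as a blinded assessment.

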### Outcome measures

Outcome measures correspond to aims as described above. The *primary outcome* will be the excess time between pediatric and ACHD care, defined as the time interval (in months) between the final pediatric visit and the first ACHD visit, minus the recommended time interval between these visits. The “recommended time” interval will be the interval suggested by the cardiologist at the final pediatric visit. For example, if the time between the final pediatric visit and first ACHD visit was 20 months but the pediatric cardiologist recommended this be 12 months, the excess time would be 8 months. If the first ACHD visit takes place before the recommended time, the excess time will be zero. For the rare study participant not having a documented “recommended time”, recommendations for frequency of care will be taken from published guidelines [22, 23]. Excess time to ACHD care is an objective and clinically meaningful outcome, as lapses between pediatric and ACHD care result in increased cardiac morbidity and need for re-intervention [9]. First ACHD appointments that occur 2 or more months later than had been recommended by the referring pediatric cardiologist will result in a review of medical records to identify potential participant or system factors, including a) ACHD waiting list too long to accommodate participant when recommended, b) ACHD team unaware of initial referral, or c) participant did not agree to an earlier appointment.

### Secondary outcomes

Given the complex, multidimensional nature of the transition process, transition interventions need to consider multiple outcomes, including cognitive factors (e.g. CHD knowledge) and self-management behaviours. Therefore, several secondary outcomes are proposed. All baseline questionnaires will be completed in the pediatric clinic, and prior to Session One for those in the intervention arm.Change in MyHeart scores between baseline, 1, 6, 12 and 18 months. The MyHeart scale consists of eight questions that assess participant’s knowledge of their cardiac condition. The MyHeart scale was developed for the CHAPTER 1 study, with a significant improvement in score observed at 1 and 6 months post intervention, compared to participants in the usual care group [16].Change in Transition Readiness Assessment Questionnaire (TRAQ) score between baseline, 1, 6, 12, and 18 months. The TRAQ is the most rigorous transition readiness scale for adolescents. Sawicki et al. identified behaviours relevant to transition, tested item reliability and validity, and then field tested the items with 194 youth with special healthcare needs [18]. Scores range from 0 to 5. Principal component factor analysis revealed two domains explaining 68 % of the total variance: self-management (16 items, mean score 3.01 ± 1.02) assessing skills such as filling prescriptions, understanding treatment side effects, and arranging medical follow-up visits; and self-advocacy (13 items, mean score 3.67 ± 0.77) assessing communication skills with the healthcare team, managing activities of daily living, and use of school and community resources. Internal consistency is high, with Cronbach’s alpha of 0.92 (Self-management) and 0.82 (Self-advocacy). A ceiling effect is unlikely given the mean scores noted above. The reading level is Grade 5.7 and this instrument takes ~5 min to complete. The 12 and 18 month assessments will provide longitudinal data on evolution of self-management and self-advocacy skills and will allow participants in the intervention group sufficient time to apply the skills gained (e.g., to independently book a physician appointment).Change in the Williams’ Scale between baseline, 1, 6, 12, and 18 months. The Williams’ scale is a measure of medical self-management and transition readiness among adolescents with special health care needs, having high internal consistency (Cronbach’s alpha 0.89) [17]. This consists of 21 Likert-scaled items and has a grade 4.9 reading level.Assessment of patient engagement via a cardiologist questionnaire. This questionnaire will be completed by the participant’s primary cardiologist at the first cardiology clinic visit (pediatric or adult site), after month 3 post enrollment. This questionnaire will help determine if those participants in the intervention group were more engaged with their cardiologist then those in the usual care group. The single-page questionnaire consists of six items and takes 1–2 min to complete.Incidence of cardiac re-intervention (surgery or interventional catheterization). Chart review at 12 and 24 months post enrollment will be done independently by two RNs who will be blinded to group allocation. This review will ascertain cardiac hospitalizations and invasive cardiac procedures (since study enrollment), confirm attendance at ACHD clinic, and identify new or progressive complications (e.g., endocarditis, heart failure, stroke, thrombosis, systemic or pulmonary emboli, arrhythmia requiring drug or procedural intervention, renal or hepatic failure) [2]. Discrepant adjudication will be resolved by a cardiologist team member.Frequency and content of verbal and written (email/text messaging/telephone) dialogue between intervention nurse and participant. The intervention RN will complete detailed post-intervention field notes after each session. Telephone communication (phone calls, text messages) and emails will be encouraged from participants at any time; all will be recorded verbatim and analyzed (see Quantitative data analysis below).
